# Bronchopulmonary Penetration of Isavuconazole in Pulmonary Transplant Recipients (PBISA01): Protocol for a Phase IV Clinical Trial With a Single Treatment Arm

**DOI:** 10.2196/37275

**Published:** 2022-09-14

**Keywords:** isavuconazole, triazoles, invasive fungal infections, fungus, fungal, infection, pharmacokinetic, bronchoalveolar lavage, bronchoalveolar lavage fluid, bronchoscopy, lung transplant, bronchopulmonary level, bronchopulmonary, epithelial lining fluid, bronchiole, alveolar macrophage, pharmaceutical, drug efficacy

## Abstract

**Background:**

Aspergillosis is the most frequently observed invasive fungal disease (IFD) in lung transplant recipients. Isavuconazole (ISA) has shown a better safety profile and noninferiority to voriconazole in the treatment of patients with IFD.

**Objective:**

The aim of this study is to describe the bronchopulmonary pharmacokinetic profile of oral ISA by analyzing the degree of penetration in the epithelial lining fluid and alveolar macrophages in patients receiving lung transplantation with a diagnosis of IFD.

**Methods:**

A total of 12 patients aged ≥18 years receiving a lung transplant with an IFD diagnosis and indication for ISA treatment and follow-up bronchoscopy will be included in the study. After 5 days of treatment with ISA and before the treatment is discontinued, the patients will be randomized (1:1:1:1) to perform the scheduled bronchoscopy at various times after the administration of ISA (2, 4, 8, and 12 hours). In total, 4 blood samples will be obtained per patient: at 72 hours after treatment initiation, on the day of the bronchoscopy, at the time of the bronchoalveolar lavage (simultaneously), and at 7 days after treatment initiation, to analyze tacrolimus and ISA plasma levels. ISA concentrations will be measured in plasma, epithelial lining fluid, and alveolar macrophages by a high-performance liquid chromatography/UV coupled to fluorescence method.

**Results:**

Enrollment for the PBISA01 trial began in October 2020 and was completed in October 2021. All samples will be analyzed once recruitment is complete, and the results are expected to be published in October 2022.

**Conclusions:**

There are no clinical studies that analyze the bronchopulmonary penetration of ISA. Bronchoalveolar lavage performed routinely in the follow-up of lung transplant recipients constitutes an opportunity to analyze the bronchopulmonary penetration of ISA.

**Trial Registration:**

European Clinical Trials Register 2019-004240-30; www.clinicaltrialsregister.eu/ctr-search/trial/2019-004240-30/ES

**International Registered Report Identifier (IRRID):**

DERR1-10.2196/37275

## Introduction

### Background

Invasive fungal diseases (IFDs) are a frequent cause of morbidity and mortality in solid-organ transplant recipients. Lung transplant recipients are especially vulnerable to the development of these infections as a result of the peculiarities of the pulmonary graft, permanent contact with the external environment, and the high levels of immunosuppression necessary for the prevention of rejection [1]. Aspergillosis is the most frequently observed IFD in lung transplant recipients [2]. Despite the universal prophylaxis with voriconazole and nebulized amphotericin B, a nonnegligible percentage of patients present with *Aspergillus* infection [3,4]. The period of greatest risk is immediately posttransplant. However, the risk is maintained throughout the posttransplant evolution.

Triazoles are effective drugs against *Aspergillus* infection. Voriconazole is the drug of first choice for the treatment of invasive aspergillosis [5,6]. However, it is not free of adverse effects.

Isavuconazole (ISA) is indicated in adults for the treatment of invasive aspergillosis and mucormycosis in patients for whom amphotericin B is inappropriate. ISA has shown a better safety profile and noninferiority to voriconazole in the treatment of patients with IFD [7] and is being increasingly used. Data from healthy volunteers demonstrated high oral bioavailability, high hepatic metabolism, and an extended elimination half-life [8].

The efficacy of ISA depends on fungal exposure to the drug and the minimum inhibitory concentration of the microorganism. To achieve the desired therapeutic effect in lung infections, it is necessary to ensure that the drug penetrates properly at the bronchopulmonary level. As it has already been shown for other azoles [9-11], the properties of ISA will greatly determine its distribution to tissues, organs, compartments, and fluids [12]. There are no clinical studies that analyze the bronchopulmonary penetration of ISA.

In this sense, the bronchoalveolar lavage (BAL) performed routinely in the follow-up of lung transplant recipients constitutes an opportunity to analyze the bronchopulmonary penetration of ISA. The simultaneous determination of the levels of ISA in plasma and the epithelial lining fluid (ELF) obtained through the BAL can be useful to determine its penetration at the bronchopulmonary level and correlate it with the response to treatment [13]. This aspect is especially relevant as lung transplant recipients are a population that is especially susceptible to the development of IFD.

### Goal of the Study

The aim of this study is to describe the pharmacokinetic profile of oral ISA at the bronchopulmonary level through the degree of penetration in the ELF in patients receiving lung transplantation with a diagnosis of IFD.

## Methods

### Design

This is a single-center, phase IV, prospective, noncontrolled, open-label, and single-arm clinical trial aimed at describing the pharmacokinetic profile of oral ISA at the bronchopulmonary level. This will be done through analyzing the degree of penetration in the ELF from lung transplant recipients diagnosed with IFD. A total of 12 patients aged ≥18 years receiving a lung transplant with an IFD diagnosis and indication for ISA treatment according to the Summary of Product Characteristics will be included in the study.

This clinical trial has been registered on the European Clinical Trials Register (2019-004240-30). This study will adhere to the SPIRIT (Standard Protocol Items: Recommendations for Interventional Trials) 2013 statement (see Figure 1 for the SPIRIT figure of enrollment, interventions, and assessments and Multimedia Appendix 1 for the SPIRIT checklist).

**Figure 1 figure1:**
[figure not shown]
Schedule of enrollment, interventions, and assessments. ELF: epithelial lining fluid.

### Ethics Approval

This study will be carried out in accordance with the principles emanating from the Declaration of Helsinki (2013) and the Oviedo Convention of the Council of Europe of 1997, ratified in 1999, and according to current legal regulations in Spain (Royal Decree 1090/2015 and EU Clinical Trials Regulation 536/2014).

The project, the final amended protocol (version 1; October 31, 2019), and the consent form have been reviewed and approved by the Research Ethics Committee at Hospital Universitario Puerta de Hierro-Majadahonda (approval 167/19) and the Spanish Regulatory Authority (Spanish Agency of Medicines and Medical Devices).

Eligible patients may only participate in the study after providing written informed consent approved by the Research Ethics Committee.

Informed consent must be obtained before performing any specific study procedure. The process of obtaining informed consent should be documented in the patient’s source documents (medical history).

### Participants and Recruitment

The patients will consecutively be enrolled from October 2020 to June 2022 in Hospital Universitario Puerta de Hierro-Majadahonda. All the patients will be hospitalized.

Before enrollment, participants will be provided with detailed information about the clinical study, including its purpose, processing, scheduling, and possible risks and benefits. All patients will be required to sign an informed written consent before any study procedures commence.

### Sample Size

In total, the inclusion of 12 lung transplant recipients is planned. Currently, there are no data in the scientific literature about the pulmonary disposition of ISA. The number of subjects has been estimated based on the objective and characteristics of the study and the drug under study. Given the descriptive nature of the study and previous similar studies [9,10], it has been considered that with the exposure of 12 subjects, the precision of the estimates will be sufficient to determine the pharmacokinetic profile of oral ISA at the bronchopulmonary level.

Patients eligible for inclusion in this study must meet all the inclusion criteria and should not meet any of the exclusion criteria (Textbox 1).

Inclusion and exclusion criteria.
**Inclusion criteria**
Recipient of a lung transplant, aged ≥18 years, with an indication of treatment with isavuconazole according to the Summary of Product CharacteristicsNo limit between the date of transplant and the date of onset of the fungal infection requiring treatment with isavuconazoleIntent and ability to follow scheduled visits, treatment plan, laboratory analysis, and other study proceduresLegally competent and able to understand, sign, and date the informed consent formSigning of the written informed consent in accordance with Good Clinical Practice and local legislation, obtained before any study procedure
**Exclusion criteria**
Allergy or intolerance to isavuconazoleContraindication for bronchoscopy or bronchoalveolar lavageAny clinical condition or analytical disorder that, in the opinion of the investigator, are considered clinically relevant to participate in the studyIndividuals who show an inability to follow the instructions or collaborate during the studyWomen who are pregnant or undergoing breastfeedingHaving participated in another clinical trial during the 3 months prior to the start of the study in which a research or commercially available drug was testedLack of intent or inability to follow the procedures described in the protocolInability to grant written informed consent

### Intervention

The trial has been approved as a “low interventional clinical trial” according to the definition in the European Clinical Trials Regulation (536/2014), because the investigational medicinal product is used in accordance with the terms of the marketing authorization, and the additional diagnostic or monitoring procedures do not pose more than minimal additional risk or burden to the safety of the subjects compared to normal clinical practice.

All participants included will receive the product under investigation—oral ISA—at the doses and dosage regimen stated in the Summary of Product Characteristics: loading dose of 200 mg/8 h for the first 48 hours and maintenance dose from day 3 at 200 mg/24 h.

After 5 days of treatment with ISA and before the treatment is discontinued, patients will be randomized to perform the scheduled bronchoscopy at different times from the administration of ISA with the following distribution:

Group 1 (n=3): 2 hours from the administration of ISAGroup 2 (n=3): 4 hours from the administration of ISAGroup 3 (n=3): 8 hours from the administration of ISAGroup 4 (n=3): 12 hours from the administration of ISA

Furthermore, 4 blood samples will be obtained per patient: at 72 hours after treatment initiation, on the day of the bronchoscopy, at the time of the BAL (simultaneously), and at 7 days after treatment initiation, to analyze tacrolimus and ISA plasma levels.

There is no restriction regarding the use of medications and concomitant therapies. All medications (except study medication) and nondrug therapies administered during the study should be listed in the corresponding section of the concomitant medication case report form (CRF). The use of any concomitant treatment will be carried out according to the authorized conditions of use or, failing that, according to the usual clinical practice.

### Outcome Measures

#### Primary End Point

The primary outcome is the measurement of ISA in the ELF. ISA concentrations will be measured in plasma ELF and alveolar macrophages by a high-performance liquid chromatography/UV coupled to fluorescence method. ISA levels in the ELF and alveolar macrophages will be obtained from the BAL. The proposed chromatographic method will allow the quantification of ISA in the clinical samples after a first step of protein precipitation and the direct injection (plasma) of resulting supernatant. For BAL samples, a previous step of sample concentration will be required to increase the sensitivity of the method. The analytical run will result in the specific characterization and robust quantification of this triazole by its UV and fluorescent profile.

Data from the cell count, percentage of alveolar cells, and volume of cell-lining fluid will be presented for the different times when bronchoscopy is performed. The volume of cell-lining fluid will be estimated using the concentration of urea in plasma and BAL from the following formula [13]: *estimated ELF volume = amount of total urea in BAL (mg) / plasma urea concentration (mg/mL)*. The area under the curve of ISA will be estimated at the ELF level. The concentration, time-dependent curves in the ELF will be calculated using noncompartmental analyses. The ratio between the ELF and plasma will be estimated from the average values of the patients included in each group.

#### Secondary End Points

For interaction evaluation, tacrolimus and mycophenolate concentrations will be determined before treatment and at 72 hours, 96 hours, and 7 days from the initiation of ISA treatment. The percentage of patients who required dose adjustment of the immunosuppressive drug after the start of treatment with ISA and the magnitude of the adjustment will be determined.

Safety will be assessed by recording adverse effects, the physical examination of patients, and analytical results.

A systematic description of all adverse events recorded during the follow-up will be performed. Listings of adverse events, previously coded by the Medical Dictionary for Regulatory Activities and grouped by organ or systems according to severity, intensity, and causal relationship with the study medicinal products, will be included.

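### The pre-treatment tacrolimus baseline is not assured to be azole-free, so in patients switched from voriconazole the isavuconazole interaction may appear attenuated, absent or reversed

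*Protocol article*

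**What the plan says.** Under Secondary End Points, the interaction is evaluated from serial levels: "tacrolimus and mycophenolate concentrations will be determined before treatment and at 72 hours, 96 hours, and 7 days from the initiation of ISA treatment". The same section adds a count, "The percentage of patients who required dose adjustment of the immunosuppressive drug after the start of treatment with ISA", together with the size of the adjustment. Under Design, the trial is uncontrolled with a single arm.

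On prior azole use, the Background begins one sentence with "Despite the universal prophylaxis with voriconazole and nebulized amphotericin B" and states in the next paragraph: "Voriconazole is the drug of first choice for the treatment of invasive aspergillosis".

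On who may enter, the inclusion criteria admit an adult lung transplant recipient "with an indication of treatment with isavuconazole according to the Summary of Product" Characteristics, at any time after transplant. Neither the inclusion nor the exclusion list mentions a previous or current azole or a washout. Under Intervention, "There is no restriction regarding the use of medications and concomitant therapies". The case report form instruction there reads "All medications (except study medication) and nondrug therapies administered during the study should be listed", which does not clearly reach a course that ended before the study began.

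Under Statistical Analysis, two analysis sets are planned, one for safety and one for pharmacokinetics. Neither is divided by previous azole.

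**The concern.** A before/after comparison without a control group isolates the effect of ISA only if nothing else acting on tacrolimus changes when ISA starts. The article's own Background makes one such change foreseeable: a patient may come to ISA from voriconazole, another triazole. That patient's baseline level may already be raised, and the baseline dose may already have been set to allow for it. The later samples then reflect the arrival of ISA and the loss of voriconazole together.

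The end point exists to show what ISA does to immunosuppressant exposure. A summary that mixes azole-free and switched patients could report a weak or absent interaction when ISA has a real one. The dose-adjustment count has the same problem, because an adjustment prompted by stopping voriconazole is recorded as one that followed ISA. Dividing levels by dose does not remove the bias, since the dose-normalised baseline is itself shifted.

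**Working it through.** The plan gives no figure for this end point, so there is nothing of its own to reproduce. The only related number is the sample size, 4 groups × 3 = 12, which agrees with the text and is not a power calculation.

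**Inputs from the article:** single arm; baseline before ISA; follow-up at 72 h, 96 h and day 7; no azole-free interval; no medication restriction; 12 patients planned, 13 enrolled.

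**Inputs that are assumptions (none is in the article):**
- a = fold rise in dose-normalised tacrolimus on ISA relative to no azole
- v = the same for voriconazole
- p = share of patients on voriconazole at the baseline sample
- the voriconazole effect is full at baseline and gone by the follow-up sample

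**Step 1, one patient.** Follow-up/baseline ratio = a/1 with an azole-free baseline, and a/v after a switch. With a = 2:
- azole-free: 2/1 = 2.0
- v = 1.5: 2/1.5 = 1.33 (attenuated)
- v = 2: 2/2 = 1.0 (no visible effect)
- v = 3: 2/3 = 0.67 (reversed)

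If v = 1 there is no bias.

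**Step 2, a mixed sample.** Geometric mean ratio = a/v^p. It equals 1 when p = ln(a)/ln(v).

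| a | v | p=0 | 0.25 | 0.5 | 0.75 | 1 | p giving ratio 1 |
|---|---|---|---|---|---|---|---|
| 2 | 1.5 | 2.00 | 1.81 | 1.63 | 1.48 | 1.33 | never |
| 2 | 2 | 2.00 | 1.68 | 1.41 | 1.19 | 1.00 | 1.00 |
| 2 | 3 | 2.00 | 1.52 | 1.15 | 0.88 | 0.67 | 0.63 |
| 1.5 | 1.5 | 1.50 | 1.36 | 1.22 | 1.11 | 1.00 | 1.00 |
| 1.5 | 2 | 1.50 | 1.26 | 1.06 | 0.89 | 0.75 | 0.58 |
| 1.5 | 3 | 1.50 | 1.14 | 0.87 | 0.66 | 0.50 | 0.37 |

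In the row a = 1.5, v = 2, the pooled effect disappears at about 0.58 × 12 ≈ 7 switched patients.

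**Step 3, the dose-adjustment count.** As arithmetic only, not a dosing rule: if the level were held constant, dose would scale by the inverse of the step 1 ratio. With a = 2 and v = 3 this is 1/2 = 0.50 for an azole-free start (a 50% decrease) and 3/2 = 1.50 after a switch (a 50% increase). In a half-and-half sample every patient is adjusted, yet the mean relative dose is (0.50 + 1.50)/2 = 1.00. The percentage and the mean size then give conflicting accounts, and neither describes ISA alone.

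**Step 4, chance of at least one switched patient.** If each of 12 patients has probability q of being on voriconazole at baseline, the chance of at least one is 1 − (1 − q)^12. This is 0.72 at q = 0.10 and 0.97 at q = 0.25. These values of q are assumptions too.

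**The case against.** Several points on the other side are sound.

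- **Prior azole status is unknown.** The two Background sentences are general. They give no duration of prophylaxis and do not say that patients are on voriconazole when ISA starts. Entry is open at any time after transplant, so some patients may be long past prophylaxis. The first-choice statement covers aspergillosis only, while ISA is also indicated for mucormycosis. A reader might infer that the baseline is in fact contaminated, or that the typical patient has just been switched. The article does not say so; it only fails to exclude it.
- **The voriconazole effect is assumed.** The article gives neither its size nor how fast it wears off. If v is below a, the result is attenuation only. A reader who took a of at most 2 and v of at least 2 would conclude that every switched patient shows no effect or a reversed one, but that follows from the chosen ranges.
- **Mycophenolate.** It is named alongside tacrolimus, so a reader might extend the argument to it. The article gives no basis for the same azole effect there.
- **The end point is descriptive and secondary.** No pooled ratio or test is named, and describing what happens when ISA is started in practice is legitimate. Subgrouping may also sit in an analysis plan that is not shown, and an azole still being given during the study would be listed.

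These points limit the claim but do not remove it. The baseline, the eligibility rules and the absence of any medication restriction are stated in the article, and the levels are taken expressly for interaction evaluation. A change on switching azoles does not answer that question, however it is summarised.

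**Conclusion.** The concern holds for tacrolimus in limited form. Followed as written, the interaction evaluation can attribute to ISA a change that is partly a switch from another triazole, because the baseline is not assured to be azole-free and there is no control group.

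The direction is clear if voriconazole raises tacrolimus at all: the ISA effect is attenuated in switched patients. It vanishes there only if the two effects are equal, and reverses only if that of voriconazole is larger. At an assumed two-fold ISA effect, the switched-patient ratio runs from 1.33 to 0.67 for voriconazole effects of 1.5 to 3, against 2.0 from an azole-free baseline. The effect on the trial's overall result depends on a share of switched patients that the article does not give.

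The primary end point, ISA in epithelial lining fluid, is not shown to be affected. The point is worth acting on because the remedy is cheap and changes what the secondary end point can conclude.

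**What to change.** 1. For every enrolled patient, abstract from the hospital chart any azole given before the first ISA dose, with drug and date of last dose. All patients were to be hospitalised, so this should be obtainable although enrolment has closed.
2. Define in advance what counts as another azole at or shortly before the baseline sample.
3. Report tacrolimus concentrations with the concurrent dose, and the percentage, direction and magnitude of dose adjustments, separately for patients with and without such exposure.
4. Attribute the change to ISA only in patients with an azole-free baseline. Describe the others as change on switching azoles. Keep both groups in the report: if prior voriconazole is common, restricting to azole-free patients alone could leave almost none of the 12 to 13.

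No change to eligibility or clinical management is needed. The cost is one retrospective data item and a sentence or two in the end point definition. The downside is small subgroups and less precision in a descriptive secondary end point.

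### Immunosuppressant levels and dose changes are summarised separately, so neither summary alone gives the size of the isavuconazole interaction

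*Protocol article*

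**What the plan says.** The interaction evaluation is in the protocol article under Methods, Secondary End Points, and has three parts.

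- **Levels:** "For interaction evaluation, tacrolimus and mycophenolate concentrations will be determined before treatment and at 72 hours, 96 hours, and 7 days" from the start of ISA.
- **Share adjusted:** "The percentage of patients who required dose adjustment of the immunosuppressive drug after the start of treatment with ISA".
- **Size of adjustment:** the same sentence goes on to say that "the magnitude of the adjustment will be determined".

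Under Intervention, the article states: "There is no restriction regarding the use of medications and concomitant therapies". Immunosuppressant doses may therefore change between the baseline sample and the later ones, and the second and third parts expect that they will. On recording, the same section says "All medications (except study medication) and nondrug therapies administered during the study should be listed" in the case report form. It does not say whether the dose and the date of each change are captured.

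The trial is described as single-arm and noncontrolled (Design), and the analysis as descriptive (Statistical Analysis). No dose-normalised concentration is mentioned, and nothing is said about how to read a level taken after a dose change.

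**The concern.** A drug level reflects both the dose given and how the body handles it. If ISA raises exposure and the dose is then lowered, the level moves back towards its starting value. The effect of ISA is then split between two quantities, the level that remains and the dose that was changed. The plan reports each by itself, and gives time points for the levels but none for the magnitude of adjustment.

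The reader of the results will want to know by how much ISA raises tacrolimus or mycophenolate exposure at a given dose. If some patients are adjusted and others not, or if adjustment is partial, the change in level is too small an answer, and the change in dose is not an answer on the same scale.

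There is a second, smaller matter. The adjustment percentage counts changes after ISA start and has no background rate beside it. Changes made for other reasons would enter the same count.

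**Working it through.** **The plan's own figures.** The article gives no numerical target, assumed effect or precision for the interaction end point, so there is no figure to reproduce. The only design number is the sample size: 4 groups × 3 patients = 12, which agrees with Sample Size and Intervention.

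**Assumed inputs (not in the documents).** R is the true ratio of exposure with ISA to exposure before ISA at equal immunosuppressant dose, taken as 1.25, 1.5 or 2.0. f is the share of the rise, on the log scale, that is offset by dose change, taken as 0, 0.5 or 1. Exposure is taken as proportional to dose.

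**Formulas.**
- Dose ratio = R^(−f)
- Raw concentration ratio = R × dose ratio = R^(1−f)
- Dose-normalised ratio = raw ratio ÷ dose ratio = R

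**Results for one patient.**

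| R | f | Dose change | Raw ratio | Dose-normalised ratio |
|---|---|---|---|---|
| 1.25 | 0 | 0% | 1.25 | 1.25 |
| 1.25 | 0.5 | −11% | 1.12 | 1.25 |
| 1.25 | 1 | −20% | 1.00 | 1.25 |
| 1.5 | 0 | 0% | 1.50 | 1.5 |
| 1.5 | 0.5 | −18% | 1.22 | 1.5 |
| 1.5 | 1 | −33% | 1.00 | 1.5 |
| 2.0 | 0 | 0% | 2.00 | 2.0 |
| 2.0 | 0.5 | −29% | 1.41 | 2.0 |
| 2.0 | 1 | −50% | 1.00 | 2.0 |

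In the half-offset rows neither the raw ratio nor the dose change equals the effect. For R = 1.5 the quotient is 1.2247 ÷ 0.8165 = 1.50. In the fully offset rows the level shows nothing and the dose change carries the whole effect.

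**Results for a cohort of 12.** Suppose k patients are fully adjusted and the rest not at all. The geometric mean raw ratio is R^(1−k/12). With R = 1.5:
- k = 0: 1.50
- k = 6: 1.22
- k = 12: 1.00

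**Can the published summaries be recombined?** Only under conditions that the article does not fix. Take k = 6 and R = 1.5. If the magnitude is summarised among adjusted patients only, the dose ratio is 0.667, and dividing gives 1.2247 ÷ 0.667 = 1.84, not 1.5. If it is the geometric mean over all 12 patients at the same time point, with unadjusted patients counted as 1, the dose ratio is 0.667^0.5 = 0.8165 and the quotient is 1.50.

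**The case against.** The strongest reply is that the plan does look at dose. A reader who stops at the percentage adjusted might infer that a real interaction could be reported as no change. The documents do not support that, because the sentence continues with the magnitude of the adjustment. In every fully offset case above, the planned output would be a stable level with all patients adjusted and a dose reduction of 20%, 33% or 50%, which reads as an interaction. This reply stands, and it limits the point to size.

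A reader might also infer that the summaries can point the wrong way. A raw level falls below baseline only if the dose is cut by more than the rise. A 30% rise is offset by a cut of 1 − 1/1.3 = 23%, so a 30% cut would give 1.3 × 0.7 − 1 = −9%. Such overcorrection is possible, but nothing in the documents suggests it. Nor does the article say that doses are titrated to hold a target level; that is inferred from its reference to adjustments being required.

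A third tempting inference is that baselines are contaminated by an earlier azole, because the Background says "Despite the universal prophylaxis with voriconazole and nebulized amphotericin B". That sentence is cited background on lung recipients generally. Nothing shows that participants were on voriconazole or were switched from it.

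It is also fair to say that a concentration-to-dose derivation is often left to an analysis plan, which is not shown here, and that the lack of a background rate follows from the declared single-arm design. Both reduce the weight of the point. They do not change the fact that the stated measures, taken one at a time, do not give the size of the interaction.

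**Conclusion.** The point holds as a minor one. Because levels and dose adjustments are reported separately while doses may change between samples, the concentration series understates an interaction that dose changes have partly offset, and its size cannot be read from either summary alone. At an assumed true ratio of 1.5, half offset, the level shows 1.22 and the dose shows −18%. Over assumed ratios of 1.25 to 2.0, half offset, the level shows 1.12 to 1.41.

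These figures rest on assumed values of R and f and on exposure proportional to dose; none comes from the documents. Detection of an interaction is not at risk, since the percentage and magnitude of adjustment are planned. The end point is secondary and descriptive, with 12 patients planned, and the primary end point is not touched.

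**What to change.** 1. **Record the dose.** Capture the tacrolimus and mycophenolate dose in force at each sample, with the date of the last change. Check first whether the concomitant medication form already holds this.
2. **Add one measure.** For each drug, compute concentration ÷ current daily dose. Summarise it as the within-patient geometric mean ratio to the pre-ISA value, with a 95% confidence interval, at 72 hours, 96 hours and 7 days. Keep the planned percentage and magnitude beside it.
3. **Flag recent changes.** The ratio assumes proportionality and a level that has settled on the new dose. With R = 1.5 and a dose ratio of 0.8165, a sample drawn before the level has responded at all would give 1.5 ÷ 0.8165 = 1.84. Flag samples taken shortly after a dose change and show the result with and without them.
4. **Word the percentage neutrally.** Call it adjustments after ISA start, since a single arm gives no background rate.
5. **Optional.** List prior azole use descriptively.

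The ratio needs the pre-ISA and 96-hour samples and the mycophenolate assay. These appear under Secondary End Points but not in the blood-sample list under Intervention, which ends "at 7 days after treatment initiation, to analyze tacrolimus and ISA plasma levels". The two lists should be reconciled.

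The cost is analysis wording and some chart review. No new patients and no change to treatment are needed, and no new samples if those under Secondary End Points were taken. The Results section says that enrollment is complete and that no ISA pharmacokinetic data had been analyzed.
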